## Abstract

**Background:**

Psychotherapy is successful for the majority of patients, but not for every patient. Hence, further knowledge is needed on how treatments should be adapted for those who do not profit or deteriorate. In the last years prediction tools as well as feedback interventions were part of a trend to more personalized approaches in psychotherapy. Research on psychometric prediction and feedback into ongoing treatment has the potential to enhance treatment outcomes, especially for patients with an increased risk of treatment failure or drop-out.

**Methods/design:**

The research project investigates in a randomized controlled trial the effectiveness as well as moderating and mediating factors of psychometric feedback to therapists. In the intended study a total of 423 patients, who applied for a cognitive-behavioral therapy at the psychotherapy clinic of the University Trier and suffer from a depressive and/or an anxiety disorder (SCID interviews), will be included. The patients will be randomly assigned either to one therapist as well as to one of two intervention groups (CG, IG2). An additional intervention group (IG1) will be generated from an existing archival data set via propensity score matching. Patients of the control group (CG; *n* = 85) will be monitored concerning psychological impairment but therapists will not be provided with any feedback about the patients assessments. In both intervention groups (IG1: *n* = 169; IG2: *n* = 169) the therapists are provided with feedback about the patients self-evaluation in a computerized feedback portal. Therapists of the IG2 will additionally be provided with clinical support tools, which will be developed in this project, on the basis of existing systems. Therapists will also be provided with a personalized treatment recommendation based on similar patients (Nearest Neighbors) at the beginning of treatment. Besides the general effectiveness of feedback and the clinical support tools for negatively developing patients, further mediating and moderating variables on this feedback effect should be examined: treatment length, frequency of feedback use, therapist effects, therapist’s experience, attitude towards feedback as well as congruence of therapist’s and patient’s evaluation concerning the progress. Additional procedures will be implemented to assess treatment adherence as well as the reliability of diagnosis and to include it into the analyses.

**Discussion:**

The current trial tests a comprehensive feedback system which combines precision mental health predictions with routine outcome monitoring and feedback tools in routine outpatient psychotherapy. It also adds to previous feedback research a stricter design by investigating another repeated measurement CG as well as a stricter control of treatment integrity. It also includes a structured clinical interview (SCID) and controls for comorbidity (within depression and anxiety). This study also investigates moderators (attitudes towards, use of the feedback system, diagnoses) and mediators (therapists’ awareness of negative change and treatment length) in one study.

**Trial registration:**

Current Controlled Trials NCT03107845. Registered 30 March 2017.

## Background

Psychotherapy is successful for the majority of patients, but a substantial proportion of the patient population does not improve or even deteriorates during treatment. Evidence suggests that between 5% and 10% of the patients leave treatment worse off than before treatment [1]. In the future, the outcome of psychological interventions could be enhanced by empirical recommendations regarding the most promising treatment strategies for a given patient (personalized predictions); as well as supplementing the traditional treatment modalities with ongoing outcome measurement and feedback or problem solving tools (personalized adaptations; [2–5]). Such prediction and treatment adaptation tools can and will likely be more easily implemented by using tools from eMental health research [6]. The more technology develops, the easier it is to implement these tools into routine care. The recent debate about precision and personalized medicine is reflected in the different purposes of such tools. While prediction tools can be seen as part of precision mental health, which tries to forecast the most promising treatment approach or strategy given specific patient characteristics, adaptation tools can be seen as part of a personalized mental health approach in which ongoing treatments are tailored to the individual patients treatment course. So far such prediction and adaptation or feedback tools have been studied independent of each other [3, 5]. However, in order to maximize the benefits of both approaches they plausibly need to be combined in a comprehensive model. The herein described trial tests such a tool which combines these two approaches in order to provide therapists with recommendations before the treatment and throughout especially for patients at risk for treatment failure.

Precision mental health has only recently received considerable attention. For example, a new method has been introduced, which aims at treatment selection based on empirical data, namely the Personalized Advantage Index (PAI; [3, 4]). Using multiple regression methods that weigh the predictive value of different patient intake characteristics, the PAI is a measure of the potential advantage of a Treatment A over a Treatment B. The use of the PAI has been shown in two applications: In the first demonstration, DeRubeis et al. used the PAI to predict which patients would profit more from CBT than an antidepressive medication (ADM) and vice versa [3]. In the second study, Huibers et al. demonstrated the PAI’s potential for the selection between cognitive therapy (CT) and IPT [4]. Another methodology was adapted for the prediction of treatment response by Lutz et al. in a sample of 618 psychotherapy outpatients [2]. In accordance with avalanche prediction models (e.g. [7]), the response curves of the most similar patients who had already been treated were used to derive a prediction for a newly incoming patient. Similarity among patients was defined in terms of Euclidean distances between the relevant predictor variables, which was also called the nearest neighbor approach (NN). The authors tested the predictive validity and clinical utility of the NN approach for treatment selection: For each patient, the authors generated predictions for two treatment protocols (CBT vs. an integrative CBT and interpersonal treatment [IPT] protocol) and compared whether one of these treatments was predicted to be more or less beneficial for a specific patient. Although, on average, no significant outcome difference between the two protocols was found, with the NN method, it was possible to obtain clinically meaningful differential outcome predictions for about one third of the patients. For the other two-thirds, the predicted change did not differ between the two protocols [2].

So far, precision mental health predictions have been only tested in post-hoc analyses. No study thus far has applied these predictions in a prospective trial in which they are provided to clinicians.

More studies have been conducted regarding adaptation of ongoing treatments based on routine outcome monitoring and feedback tools. Several international research groups investigated such tools (mostly feedback systems) in randomized controlled trials (RCT). The first three RCTs in that field found that feedback to therapists on patients’ progress was effective in improving patient outcomes, particularly for those patients who showed an increased risk for treatment failure (not on track patients; NOT). The percentage of patients at risk for treatment failure receiving feedback and reaching a reliable or clinical significant improvement was about 14% higher than the rate for the NOT patients without feedback [8–10]. Furthermore, those NOT patients with feedback had an 8% lower deterioration rate than without feedback. Additionally, feedback to therapists of NOT patients led to, on average, longer treatments. However, it led to shorter treatments, on average, for on-track (OT) patients. Those early investigators came to believe that the essential value of feedback systems was to help clinicians become aware of pending treatment failure, something that they could not achieve through clinical intuition [11].

To date, key findings of these original studies have been replicated under different conditions in many investigations and have been reported in four systematic reviews [12–15] and five meta-analyses [16–20]. For example, in a recent review on the effects of feedback Krägeloh and colleagues (2015) report that of the 25 identified studies, 17 showed a significantly positive feedback effect on average or for NOT patients [14]. More detailed information about the size of the effects derive from several meta-analyses [17, 18, 20]. In these studies the significant effect sizes regarding improvement for NOT patients with feedback vs. treatment as usual (TAU) varied between an effect size of g = .22 and g = .53. However, a recent Cochrane report graded the quality of evidence for these effects as low and requests further studies with stronger designs [20]. When clinical support or problem solving tools (CST) were implemented the effect size for NOT patients increased and reached g = .70 [18]. CST’s help to determine the potential cause of deterioration and provide clinical suggestions to adapt or improve treatments at risk for failure.

From this cumulative body of research it can be concluded that feedback is effective for NOT patients especially in combination with CSTs. However, most feedback studies were conducted within settings with relatively short treatments provided to moderately impaired patients (e.g., college counseling centers; [15, 18, 19]. Recent studies investigated feedback effects in more disturbed outpatients [21, 22], in psychosomatic in-patients [23, 24], patients with eating disorders, PTSD, patients with substance use disorders, depression and anxiety disorders [21–25]. No study so far has investigated diagnostic group as a moderator of the feedback effect.

De Jong et al. [21] found substantial differences between therapists in their use of feedback. Having a higher commitment to use the feedback showed to be significantly associated with a higher probability to use the feedback and therapists who indicated to use the feedback showed to be more effective for patients with a risk of treatment failure (NOT patients). Additionally, therapists who were more committed to use the feedback at the beginning of the study had patients who progressed faster in treatment. Similarly, Knaup et al. [16] found in a meta-analysis of 12 feedback studies that the frequency of feedback given in the studies as well as the kind of feedback (progress vs. status) seem to be promising moderators. Furthermore, Lutz, Rubel, Schiefele, Zimmermann, Böhnke, and Wittmann [26] found that patients’ as well as therapists’ attitudes towards feedback combined with the use of the feedback system was significantly associated with treatment outcome. Those therapists, which had a positive attitude related the feedback system and did respond with specific actions did show the best effect sizes, whereas therapists with a negative attidude but many, probably uncoordinated, actions had the worst effect sizes.

Treatment length is the most studied mediator variable. In this context one finding was that patients with negative feedback (NOT) stayed longer in treatment while patients with positive feedback (on track; OT) had fewer sessions in comparison to therapies where no feedback was provided [27]. This finding suggests that the effects of feedback on treatment outcome might be mediated by treatment duration. However, the effect of feedback on number of sessions was not consistently found [16, 20, 23, 28]. Therefore, a further investigation whether feedback influences the length of treatments and in which way this might be connected to the effects of feedback on outcome is needed.

In summary, the described studies on psychometric feedback have specific strengths and weaknesses. While in most RCTs the high frequency of repeated measurements in the feedback as well as in the control conditions can be evaluated positively, studies often included treatments with few sessions and moderately impaired patients [19]. Further weaknesses are that past studies did not include structured diagnosis or the control of treatment adherence. Also most studies were restricted to commercial feedback systems and did not include prediction or treatment selection tools.

Furthermore, above described moderators and mediators were found with post-hoc analyses as a by-product of explorative analyses in different studies. No specific power analyses was conducted to study these effects and they have not been studied in a comprehensive model within the same study.

## Objectives

### Primary research questions and hypotheses

The primary objective of the current project is to investigate several questions of personalized psychotherapy research with two personalized feedback intervention groups (IG1: Feedback; IG2: Feedback plus CSTs (including personalized predictions before the start of the treatment and adaptation tools during treatment) and one control group (CG) with repeated measurements. As such, this is the first study that prospectively tests the effects of personalized treatment recommendations and adaptation tools. Moreover, it adds to previous feedback research a stricter design by investigating another repeated measurement CG as well as a stricter control of treatment integrity. It also includes a structured clinical interview (SCID) and controls for comorbidity (within depression and anxiety disorders). Furthermore, a severely impaired patient sample is studied and an international outcome instrument is used. This study also investigates the above described moderators (attitudes towards, use of the feedback system, diagnoses) and mediators (therapists’ awareness of negative change and treatment length) in a comprehensive model and in one study.

Therefore, the study allows for testing the following hypotheses:Main hypotheses:H1: *NOT patients in the feedback condition (IG1) show on average better treatment outcomes than NOT patients in the CG.*
H2: *NOT patients in the IG2 (+personalized prediction and adaptation tools) show on average better treatment outcomes than NOT patients of the IG1 (no tools but psychometric feedback).*

Secondary hypotheses concerning moderators and mediators (see also Fig. 1):H3: *The positive impact of feedback for NOT patients is* moderated *through the usage of the feedback system and/or the attitudes of the therapist towards feedback.*

*H3a: The more frequently and the longer feedback is used, the more aware are therapists for negative change.*

*H3b: The more positive the therapists’ attitudes towards feedback, the more aware are therapists for negative change.*

*H3c: The effects of feedback on patient outcomes do not differ between diagnostic groups (depression and anxiety).*

H4: *The positive impact of feedback for NOT patients is* mediated *through therapists’ awareness of negative change as well as treatment length.*

*H4a: The positive impact of feedback for NOT patients is mediated by the therapists’ awareness of negative developments of their patients.*

*H4b: The positive effect of therapists’ awareness on treatment outcome is mediated by treatment length (number of sessions).*

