### Implementation of feedback and clinical adaptation and support tools

Each therapist is able to login after each session to the online feedback portal to get an overview about status and progress of his/her patient in the intervention groups (IG1 & IG2). For patients of the IG1, therapists are provided with information about the initial status concerning symptoms (BSI & OQ-30), interpersonal functioning (IIP-32 & OQ-30) as well as diagnoses specific symptoms (GAD-7 or PHQ-9). Beside the status measures, also individual progress information on the symptom level (HSCL-11 each session) is provided to the therapist (see line with dots in Fig. 3). Higher values indicate more distress. The gray curve represents the expected treatment response for this specific case based on growth curve models developed for the nearest cases (nearest neighbors). Additionally to the expected treatment response (gray curve) a black signal curve beginning from session 5 is displayed (90% confidence boundary). This curve will be recalculated after each session considering the already made progress up to this point. When a patient lies above the black curve (90% confidence boundary), a warning signal is presented within the feedback system.

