**Fig. 5 Fig5:**
[figure not shown]
Example screenshot from the feedback system in the IG2. All orange signals within the box are linked to respective adaptation and problem solving tools. For therapists in the IG1 neither the signals in the red box nor the access to the tools will be included

Therapists of the IG1 will be able to see status and progress reports as described above (including an overall evaluation of progress in the HSCL, but not expected treatment response and the confidence boundary) whereas the IG2 will get additional access to CSTs implemented in the system. The CSTs are divided into two main areas: a personalized treatment recommendation module and a personalized treatment adaptation module.

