### Personalized treatment recommendation

The personalized treatment recommendation is available at the beginning of treatment. The therapists will be provided with important information for their patients on different domains like risk for suicidality, substance abuse, treatment expectation, drop-out risk, symptomatology, and interpersonal functioning.

Additionally, a treatment recommendation for the early phase of treatment is given (Fig. 4). Already treated similar cases within the outpatient center are selected. Therapists rated whether they chose a more problem-solving focused approach, a more motivation-oriented approach or a mixed approach for these cases based on session reports. Based on the closest cases of already treated patients with those three strategies an effect-size is calculated for each of the three interventions. Thus, therapists receive a recommendation which early treatment strategy might lead to the best treatment effect for this particular case. The ten closest cases are depicted in another graph with their treating therapist. This leads to the opportunity that therapists are able to contact therapists who already treated similar cases for peer-supervision.

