### Personalized treatment adaptation

To make sure that adaptation and support tools are addressing the right domains in the course of treatment, the Assessment for Signal Clients (ASC) as well as the Affective Style Questionnaire (ASQ) are measured every fifth session (Fig. 5). The four subscales of the ASC are used to measure therapeutic alliance, motivation, social support, and life events. Based on a cut-off value for each measure “orange” (in Fig. 5 light grey) or “green” (in Fig. 5 dark grey) signals are provided for patients who were identified as on risk for treatment failure. The ASQ is used as a marker for the extent of the emotional regulation ability of the patient with the same purpose. If orange signals are detected on one of the five scales (ASQ and/or ASC) then the therapist is able to click on the scale and to open a website with more information on those tools for a specific domain. This additional specific clinical guidelines are oriented on the Clinical Support Tools developed by Lambert et al. and are translated and adapted to the German outpatient setup [5]. Those original tools are extended by using additional clinical as well as video and audio material. Prior to the beginning of the project, participating therapists are instructed and trained on the new feedback portal by the research associate of the project and a video clip, which explains the system.

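### The recommendation reaches IG2 patients before not-on-track status is known, but the only hypothesis that includes it is confined to not-on-track patients and the archival comparison group

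*Protocol article*

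**What the plan says.** The Background gives the gap to be filled: "No study thus far has applied these predictions in a prospective trial in which they are provided to clinicians". The Objectives then state that "this is the first study that prospectively tests the effects of personalized treatment recommendations and adaptation tools". The Discussion describes the primary objective as the effect of prediction and adaptation tools on outcome in routine outpatient care. Neither statement of the objective restricts it to NOT patients.

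Under Implementation of feedback and clinical adaptation and support tools, the material that only IG2 receives is divided into "a personalized treatment recommendation module and a personalized treatment adaptation module". The two differ in timing and target:
- **Recommendation:** "The personalized treatment recommendation is available at the beginning of treatment", and it concerns the early phase of treatment.
- **Adaptation:** "signals are provided for patients who were identified as on risk for treatment failure". In the progress display, "a black signal curve beginning from session 5 is displayed".

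H2 is the only hypothesis that includes the recommendation. It states that NOT patients in IG2 "show on average better treatment outcomes than NOT patients of the IG1 (no tools but psychometric feedback". H1 compares IG1 with CG in NOT patients. H3 and H4 concern moderators and mediators of feedback. According to Randomization, only CG and IG2 are randomised; IG1 is matched from archival data.

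**The concern.** The objective and the hypotheses cover different populations. The objective speaks of the tools' effect on outcome. H2 speaks of patients who have gone off track. For the adaptation tools the two agree, because those tools are directed at patients flagged as at risk. For the recommendation they do not: it is delivered before anyone can be flagged, so it reaches IG2 patients who will later be on track as well as those who will not.

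This has two consequences. First, patients who received a recommendation and stayed on track contribute to no test of it. Second, NOT status is observed after the recommendation has had the chance to work. If a good recommendation keeps some patients on track, they leave the IG2 side of H2, and the NOT patients who remain are a more adverse selection than those in IG1. The H2 contrast can then differ from the recommendation's effect even if the matching of IG1 is perfect.

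Meanwhile the comparison that randomisation protects, IG2 v CG, appears in no hypothesis. At stake is whether the report can say anything about recommendations beyond the package's effect in the NOT subgroup.

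**Working it through.** **1. The plan's own figures** (Sample size calculation and data analyses). For H2: d = .30, so f = .15; correlation .4; two groups, two times. With the repeated-measures group-by-time noncentrality λ = f² × N × 2/(1 − .4), N = 108 gives λ = .0225 × 108 × 2/.6 = 8.1 and power .805. The stated 108 reproduces. Then 54/.4 = 135 per intervention group and 27/.4 = 67.5, rounded to 68, for CG; 135 + 135 + 68 = 338. Multiplying by 1.25 gives 169, 169 and 85. The point rests on no arithmetic error.

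**2. Share of IG2 outside H2.** The NOT rate is 40% (assumed by the plan), 49% or 56% (the earlier studies it cites).

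| NOT rate | In H2, of 135 | Outside H2, of 135 | Outside, of 169 recruited |
|---|---|---|---|
| 40% | 54 | 81 (60%) | 101 |
| 49% | 66 | 69 (51%) | 86 |
| 56% | 76 | 59 (44%) | 74 |

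**3. Illustration of selecting on NOT status.** Assumed, since the documents give no values: standardised early and final scores correlated .6; a fixed NOT cut-off that flags 40% without the recommendation; a recommendation that improves both scores by .30 SD.
- Without it: cut-off .253; mean early score among NOT patients .386/.40 = .966; mean final score .6 × .966 = .580.
- With it: a patient is NOT only if the untreated early score exceeds .253 + .30 = .553, which leaves 29%. Mean untreated early score .342/.290 = 1.180; mean final score .6 × 1.180 − .30 = .408.
- NOT-only difference: .580 − .408 = .17 SD, against a true .30.

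For true benefits of .20 and .50 SD, simulation under the same assumptions gives .12 and .28. The size depends on the assumptions. What matters is that the two quantities need not agree.

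**4. What an all-patient IG2 v CG comparison could detect.** Two-sided 5%, 80% power, standardised difference at one time point: d = 2.80 × √(1/n₁ + 1/n₂). Adjusting for the first score at r = .4 multiplies this by √(1 − .16) = .917.
- 68 v 135: 2.80 × .149 = .42; adjusted .38.
- 85 v 169: 2.80 × .133 = .37; adjusted .34.

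The noncentral t distribution gives the same values to two decimals. For d = .30 with 68 v 135, power is .52 unadjusted and .59 adjusted. The r = .4 is the plan's pre/post value; the correlation between early HSCL-11 scores is not given.

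These figures are on a different scale from the plan's group-by-time calculation, which would return .97 for 203 patients at f = .15 (equal groups). The two sets should not be compared.

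**The case against.** The strongest reply is that the trial says openly that it tests a combination. The Abstract refers to a comprehensive feedback system, the Background says the two approaches should be combined, especially for patients at risk, and H2's own label names prediction and adaptation tools together. The sentence claiming novelty also joins the two. This stands. A reader might infer that the plan is wrong because it never separates the recommendation from the adaptation tools, or that its objective goes wholly unanswered. The documents support neither: a package test is a legitimate, declared choice, and H2 does address that package in NOT patients.

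A reader might also infer that IG2 v CG up to session 5 would isolate the recommendation, because the signal curve starts only then. It would not. IG2 therapists also have status and progress feedback and start-of-treatment information on risks such as drop-out. Table 1 schedules the questionnaires behind the adaptation signals at the beginning as well as every fifth session. The article does not define the early phase as sessions 1 to 5. Inclusion requires only three sessions, so some patients may have no session-5 score. The same therapists treat both groups, and the plan itself anticipates that support material may be used with control patients, which would dilute a difference.

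Finally, extra secondary analyses are often left to a full protocol or SAP, which is not shown. That is fair for analysis detail. It does not remove the mismatch between an objective and hypotheses that are both fixed in this article.

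**Conclusion.** The point holds as a mismatch of population and contrast. The stated objective is not limited to NOT patients. The recommendation precedes NOT status and may influence it. The single hypothesis that includes it is confined to NOT patients and to a non-randomised comparison group. Between 44% and 60% of IG2 patients enter no test of the recommendation; 60% is the upper end, because the plan calls its 40% NOT rate conservative. The randomised contrast is used by no hypothesis.

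The point does not extend to saying that bundling is an error, that the package objective is unanswered, or that any contrast in this design identifies the recommendation alone. The attenuation from .30 to .17 SD is an illustration under assumed values, not an estimate for this trial. H2 remains usable, provided its conclusion is worded for what it estimates.

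**What to change.** 1. **Wording.** State that H2 estimates the effect of the combined package in NOT patients, and limit conclusions about recommendations accordingly. This costs nothing.

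2. **One pre-specified secondary comparison.** Compare IG2 with CG in all randomised patients, adjusted for the first HSCL-11 score. Use the per-session HSCL-11 in a mixed model with the therapist random effect already planned, so that patients with fewer than five sessions contribute. Report both the early phase (sessions 1 to 5) and the end of treatment. Label the early result as feedback plus recommendation and the end result as the whole package; neither is the recommendation alone. No new data are needed. The cost is limited sensitivity: detectable d is about .38 to .42 with 68 v 135, or .34 to .37 with 85 v 169, and spill-over through shared therapists may reduce the difference. It should therefore stay secondary.

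3. **IG2 v IG1 in all patients** is at most a non-randomised supporting analysis. The section on implementing the feedback tools must first be reconciled: its opening text describes the expected-response curve and boundary for IG1, while the text after Fig. 5 says IG1 therapists did not see them. Until that is settled, it is unclear which components separate the two groups.
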